### **Process evaluation—optimizing the intervention**

A random sample of participating patients will be asked a series of additional, structured questions at the time of outcome assessment 90 days post-STEMI. Specifically, a 20% random selection of patients who received the intervention will be sampled, equating to approximately 80 patients. In addition, all family physicians in the intervention group will be mailed a one-page questionnaire along with the second iteration of the provider letter (month five post-STEMI). A response rate of only 15% will allow us to get feedback from about 50 family physicians. The questionnaires to both patient and provider assess acceptability of the intervention and the reasons for any (lack of) action taken (See Additional file 2: Appendix D for patient process evaluation questionnaire and Additional file 2: Appendix E for provider process evaluation questionnaire**)**. The answers to these questionnaires will be summarized descriptively and used to inform future iterations of the intervention.

We also plan to conduct focus groups with both patients and providers to better understand both why the intervention did (or did not) work and how it might be optimized. Participants for these focus groups will be purposively recruited based on the responses to the questionnaires. We plan to conduct one or two focus groups of six to eight patients and one focus group of four to six physicians, each group lasting about one hour occurring at the HIU. These focus groups will follow a semi-structured guide that will be informed by the issues identified in the questionnaires. The overarching goal of the focus groups will be to compare and contrast various designs and approaches of sending reminders to decrease the risk of inappropriate medication discontinuation. To this end, a variety of reminder designs will be handed out among the focus group participants to encourage discussion (similar to how marketing firms traditionally have used focus groups). Physician participants will be provided with $75 (and refreshments). Patient participants will be offered a $25 gift certificate (and refreshments) as remuneration for attending the focus group. The sessions will be recorded and transcribed verbatim.

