### **Allocation**

The randomization schedule was computer-generated by a statistician independent of the study, using a permuted block design with randomly varying block lengths of four, six, or eight. Eligible patients are randomly allocated to one of the two treatment arms. Although enrolment of more than one patient treated by a particular family physician is expected to occur infrequently, randomization will be carried out to ensure that, once a patient from any family physician is randomized, all future patients seen by that family physician will automatically be assigned to the same arm. This is necessary to avoid contamination (with one family physician having patients in different intervention arms). Roughly one-half of patients will be allocated to each study arm (the actual allocation ratio will depend on the size of the clusters). Based on pilot data, we anticipate that approximately 10% to 15% of patients will not have a family physician. In keeping with the pragmatic design of the trial, a patient without a family physician will be included (receiving only the patient-level intervention).

Randomization is delayed by one week (after the angiogram) to permit time to identify and exclude patients with in-hospital death. Randomization will continue until the target sample size is achieved. The anticipated duration of enrolment is 15 months. The allocation sequence will be concealed from the investigators and outcome assessors; only the study coordinator who will be sending out the letters will have access to the un-blinded allocation list.

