### **Data collection**

Baseline patient characteristics will be obtained from standard patient-registry information at the HIU. This includes demographic information, comorbidities, and the findings at the time of angiography.

Outcomes will be assessed 3 and 12 months post-index angiogram through patient phone calls by a research coordinator associated with the HIU who will be trained expressly for this function. The research coordinator conducting the phone calls will not have access to the allocation list. The calls are made on behalf of the treating cardiologist at the HIU, and all patients will be encouraged to review cardio-protective meds with their family physician. The phone call follow-ups will ask patients to list their current, daily medications (and doses) without specific prompting in order to reduce bias. Attempts will be made to contact patients for a maximum of 30 days prior to being considered lost-to-follow-up. Reasons for loss-to-follow-up will be tracked.

For a sample of patients aged 65 and older, the Ontario Drug Benefit database will be used to examine the accuracy of the self-reported primary outcome and to further evaluate adherence using the medication possession ratio over the preceding year, which has been shown to be associated with both pill counts and clinical effects [47].

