### **Limitations**

Although our overall goal is to improve adherence to medications, it is important to note that our primary outcome evaluates discontinuation (or ‘persistence’). This represents the most extreme form of non-adherence. The allocation is clustered at the level of the family physician to limit contamination, but it was deemed not feasible to do the same with pharmacists. Although the tear-away page in the patient letter for pharmacists could theoretically bias toward a null finding if pharmacists transfer their learning from one patient to another, we considered this risk to be small in comparison to the potential benefit of facilitating interactions with these key primary care providers.

It is important to note that this trial will not be able to discern the relative importance of intervention at patient versus family physician level. A larger sample size would be preferable to provide an opportunity to test multiple ways of designing and delivering this type of intervention within a single trial. In the case of a positive effect, the pragmatic approach utilized will not allow for inferences regarding the ‘most important’ active ingredients in the intervention. We intend to explore these issues through the process evaluation. The questionnaires developed for the process evaluation are not independently validated for assessing acceptability and usability of the reminder intervention. However, they will be evaluated qualitatively to inform iterative improvements to the program after the trial is completed, and will allow us to identify interested participants for focus groups.

Although the research coordinator conducting the outcome assessment will be blinded to allocation, it is possible that some patients will discuss receiving the intervention with the coordinator. Another important caveat is that we will be using patient self-report for main outcome measurements—an approach which has previously been used in a similar trial [38]. We are planning to evaluate the validity of self-report data in our study by comparing patient reported medication use (including the MMAS) with data recorded in administrative databases for a subsample of participants above age 65 (for whom data are accessible using the Ontario Drug Database). Through these administrative databases, we can also pursue proxy measures for adherence (rather than strictly discontinuation) by assessing the medication possession ratio.

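### Process-evaluation questions put only to intervention patients at the 90-day outcome assessment can reveal about 20% of that arm to the blinded outcome-assessor role before the 12-month primary outcome

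*Protocol article*

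**What the plan says.** Blinded outcome assessment is claimed in the Abstract and under Study design, and Limitations repeats that the coordinator who assesses outcomes is blinded. Three sections of the protocol article set out how this is protected.

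- Allocation: "only the study coordinator who will be sending out the letters will have access to the un-blinded allocation list".
- Data collection, on who calls: "Outcomes will be assessed 3 and 12 months post-index angiogram through patient phone calls by a research coordinator associated with the HIU".
- Data collection, on the safeguard: "The research coordinator conducting the phone calls will not have access to the allocation list".

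The section on the process evaluation adds a task at the first of these assessments: "A random sample of participating patients will be asked a series of additional, structured questions at the time of outcome assessment 90 days post-STEMI". It then narrows the sample to one arm: "a 20% random selection of patients who received the intervention will be sampled, equating to approximately 80 patients". On content it says: "The questionnaires to both patient and provider assess acceptability of the intervention and the reasons for any (lack of) action taken".

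Limitations mentions one way in which blinding may fail: "it is possible that some patients will discuss receiving the intervention with the coordinator".

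**The concern.** Only intervention patients can be selected for these questions, so a selection flag is in effect a partial allocation list. The content also gives the arm away, because it asks about letters that control patients never receive. If the person making the outcome call is given the flag or asks the questions, the stated safeguard no longer works for those patients.

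The timing matters because the 90-day call comes before the 12-month primary outcome. Placing the process questions after the 3-month outcome items would protect the 3-month data but not the later call. The primary outcome is self-reported by telephone and scored all-or-none over four medication classes, so one class missed or followed up can change a patient's result. The 12-month call also collects the Morisky score, stopping because of side effects, and discussion with the family physician. By this route the knowledge arises in one arm only, so any effect on the recorded data would not be shared equally between the arms.

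**Working it through.** **1. Who is sampled.** Inputs: 815 randomized (Sample size); roughly half to each arm (Allocation); 20% sampled (Process evaluation).

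- Intervention arm only: 0.20 × 815/2 = 0.20 × 407.5 = 81.5. This reproduces the article's figure of about 80.
- Both arms: 0.20 × 815 = 163. This does not fit.

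The stated count therefore confirms that only the intervention arm is sampled.

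**2. How many reach the primary analysis.** Input: 80% participation at 12 months (Sample size).

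- Sampled patients analysed: 81.5 × 0.80 = 65.2, about 65.
- Intervention patients analysed: 652/2 = 326.
- Share of the intervention arm: 65.2/326 = 20%. Share of all analysed patients: 65.2/652 = 10%. Share of controls by this route: 0%.

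**3. Whether the article keeps the caller apart from the sample.**

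| Question | What the article gives |
|---|---|
| Who makes the 3- and 12-month calls? | A research coordinator, without access to the allocation list |
| When are the process questions asked? | At the 90-day outcome assessment |
| Who asks them? | Not stated (passive wording) |
| Separate interviewer? | None described |
| Matched questions for controls? | None described |
| Different caller at 12 months, or flag hidden then? | Not described |
| Is this route acknowledged? | No; only disclosure by patients is |

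**4. What a bias could do (illustration).** Assumption, not in the documents: knowing the arm shifts the recorded primary outcome by 5 to 10 percentage points among these patients, all in one direction.

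- Shift in the arm difference: 0.20 × 5 = 1 point, to 0.20 × 10 = 2 points.
- Against the planned 11-point difference: 1/11 = 9%, to 2/11 = 18%.
- Standard error of the difference with 50% in both arms: √(2 × 0.25/326) = 0.039, or 3.9 points.
- A 1-point bias is 0.01/0.039 = 0.26 standard errors. Type I error = P(Z > 1.70) + P(Z < −2.22) = 0.045 + 0.013, about 5.8%.
- A 2-point bias is 0.02/0.039 = 0.51 standard errors. Type I error = P(Z > 1.45) + P(Z < −2.47) = 0.074 + 0.007, about 8%.

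These are against a nominal two-sided 5%. Applying the article's variance inflation factor of 1.02 makes the standard error √1.02, or about 1%, larger and hardly changes the results.

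**The case against.** The strongest reply is that the key steps are inferred. The article does not say who asks the process questions. Drawing the sample needs the allocation list, so an unblinded person must be involved, and that person might also ask the questions. The full protocol and the questionnaire appendix are not shown and may settle this. Nor does the article say that one individual makes both calls. Even if one does, about 65 patients would have to be remembered, or still be flagged, nine months later among about 652. These points stand, and they are why the concern is about what the role can learn and not about what a given caller will know. They do not remove it: the questions are placed at an assessment for which only the blinded role is named, and nothing described keeps the two apart.

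It can also be said that patients list their medications unprompted, which limits probing, and that self-report is checked against dispensing records. The first point reduces the scope for bias. The second helps little: the check covers 138 patients aged 65 or over and measures overall agreement, not error that differs by arm.

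A reader might infer several stronger points that the documents do not support:

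- That the claim of blinded assessment is simply false. By this route about 90% of patients are unaffected, and for the rest the breach depends on who asks the questions.
- That the caller codes the drugs into classes. The article does not say who does this.
- That intervention patients get an extra contact. The questions fall at an assessment that both arms have.
- That the focus groups add to the problem. The article gives them no date.
- That the comparison is biased in a known direction. Nothing in the article establishes one.

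**Conclusion.** The concern holds in a limited form. Followed as written, the process evaluation lets the outcome-assessor role learn the allocation of about 80 intervention patients before the 12-month primary outcome. About 65 of them would be analysed, which is 20% of that arm, against no controls by this route. Limitations does not acknowledge this, because it covers only what patients may volunteer.

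The conclusion rests on two readings: that the role named for the 3-month call also asks the questions placed there, and that knowledge gained then can carry over to the 12-month call. Both are natural readings, but neither is stated. The effect on the result cannot be known from the documents. The range of 1 to 2 points, with a type I error of about 5.8% to 8%, depends wholly on the assumed 5-to-10-point shift and serves only to show scale. The change should be made, since it is cheap and protects a stated design feature, but the point does not invalidate the trial.

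**What to change.** Take the patient process questionnaire out of the blinded 90-day call, in one of three ways:

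1. Mail it, as is already planned for the family physicians.
2. Ask it after the 12-month outcome fields are locked, with the selection flag hidden from the caller until then.
3. Have the study coordinator who sends the letters, and who is already unblinded, administer it.

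In each case withhold the list of sampled patients from the outcome caller, and state in the article who asks the questions.

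The cost is small. Mailing may lower the response, and waiting until 12 months delays feedback on the early letters and loses some recall. The trial itself does not depend on having these data at 90 days: they are to be summarized descriptively and used to improve later versions of the intervention once the trial is over.

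If the questions stay in the 90-day call, qualify the blinding claim in the Abstract, Study design and Limitations to say that it does not cover the sampled intervention patients.

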## Discussion

Discontinuation of cardiac medications post-STEMI occurs due to patient, provider, and system-level factors and has important consequences for the patient. This two-arm, pragmatic, cluster-randomized controlled trial will test whether mailed reminder letters sent from the interventional cardiologist to the patient and their family physician can successfully increase adherence. Even if the trial does not show a significant effect on medication discontinuation, the embedded process evaluation will provide helpful information for planning future interventions aiming to address this important issue.

### **Limitations**

Although our overall goal is to improve adherence to medications, it is important to note that our primary outcome evaluates discontinuation (or ‘persistence’). This represents the most extreme form of non-adherence. The allocation is clustered at the level of the family physician to limit contamination, but it was deemed not feasible to do the same with pharmacists. Although the tear-away page in the patient letter for pharmacists could theoretically bias toward a null finding if pharmacists transfer their learning from one patient to another, we considered this risk to be small in comparison to the potential benefit of facilitating interactions with these key primary care providers.

It is important to note that this trial will not be able to discern the relative importance of intervention at patient versus family physician level. A larger sample size would be preferable to provide an opportunity to test multiple ways of designing and delivering this type of intervention within a single trial. In the case of a positive effect, the pragmatic approach utilized will not allow for inferences regarding the ‘most important’ active ingredients in the intervention. We intend to explore these issues through the process evaluation. The questionnaires developed for the process evaluation are not independently validated for assessing acceptability and usability of the reminder intervention. However, they will be evaluated qualitatively to inform iterative improvements to the program after the trial is completed, and will allow us to identify interested participants for focus groups.

Although the research coordinator conducting the outcome assessment will be blinded to allocation, it is possible that some patients will discuss receiving the intervention with the coordinator. Another important caveat is that we will be using patient self-report for main outcome measurements—an approach which has previously been used in a similar trial [38]. We are planning to evaluate the validity of self-report data in our study by comparing patient reported medication use (including the MMAS) with data recorded in administrative databases for a subsample of participants above age 65 (for whom data are accessible using the Ontario Drug Database). Through these administrative databases, we can also pursue proxy measures for adherence (rather than strictly discontinuation) by assessing the medication possession ratio.

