## Objectives

The overarching goal of this project is to improve long-term use of secondary prevention medications for patients with CAD, and thereby reduce cardiovascular events through the use of an easily generalizable and sustainable intervention. The primary objective of this study is to assess if repeated mailing of an educational message and reminder to the family physician and the patient will decrease the proportion of patients who discontinue evidence-based secondary-prevention medications at twelve months post-STEMI. A secondary objective is to encourage cardiac patients and their primary care providers to discuss the benefits of long-term adherence to cardiac medications.

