### **Participants and Setting**

In Ontario, healthcare is financed through a single-payer (publicly administered) system. There are no co-payments for visits to generalist or specialist physicians or for care provided in hospitals for patients of any age, and almost all licensed prescription medications are covered for patients 65 and over. Patients younger than 65 years pay for medications out-of-pocket or through private insurance plans, or are covered by the provincial plan if they qualify for social support.

In this study, eligible patients are adult patients (>18 years) with a diagnosis of STEMI, who undergo a coronary angiography procedure (with or without angioplasty), at the Heart Investigation Unit (HIU) in Hamilton, Ontario, and who are alive at hospital discharge. In keeping with the pragmatic approach to study design, no other exclusion criteria will be applied. The HIU is the only catheterization lab in its region, with a catchment population of almost 1.5 million people. More than 700 STEMI patients undergo an angiogram there each year. Studies at the HIU have highlighted excellent rates of prescribing of evidence-based therapies at discharge post-STEMI, but substantial reduction in use starting three months following discharge [39,40]. While 78% of STEMI patients leave the HIU taking a statin, an ACE-inhibitor (or ARB), a beta-blocker, and aspirin, by 90 days the proportion still taking all four of these medication classes falls to 63% (unpublished data from the Strategic Management of Acute Reperfusion and Therapies in Acute Myocadial Infarction (SMART-AMI) study).

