### **Outcomes**

The primary outcome is the proportion of living patients who describe taking all cardiac medication classes of interest measured at twelve months. This type of ‘all-or-none’ measure has been recommended for evaluating quality improvement interventions, especially related to medication utilization [43]. Specifically, we will assess whether patients are taking a statin, beta-blocker, angiotensin modifier (ACE or ARB), and aspirin at twelve months. All STEMI patients have reasonable evidence supporting these medications [3]; we anticipate that randomization will balance those patients for whom evidence is less clear or who might have contraindications to any of these medications.

We will also assess whether patients are taking these four medication classes plus a secondary antiplatelet (clopidogrel, prasugrel, or ticagrelor) at three months. Therefore, patients at three months will be dichotomized as to whether or not they are taking all five cardiac medication classes, and at twelve months they will be dichotomized according to whether they are taking all four relevant medication classes. The difference in the number of medication classes considered at three and twelve months relates to uncertainty in the evidence regarding the appropriateness of a secondary antiplatelet at this timeframe. Additional secondary outcomes include a comparison of: the proportion of patients who report actively taking each cardiac medication class of interest (item-by-item) at three and twelve months; the proportion of patients who report stopping medications due to side effects at three and twelve months; the proportion taking one or two or three medication classes concurrently at three and twelve months; and the proportion of patients with a perfect Morisky Medication Adherence Score (MMAS) for cardiac medication compliance at three and twelve months. The MMAS is a brief, standardized adherence questionnaire which excellent reliability [44], and has been shown to be predictive of cardiovascular medication adherence [45] and to be associated with control of blood pressure and cholesterol [44,46]. In addition, all patients will be asked at three months and twelve months whether they had a discussion with their family physician during past three months in which the provider had encouraged long-term cardiac medication compliance.

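### The primary outcome measures use of all four drug classes at twelve months, but the Objectives and Limitations sections describe it as discontinuation

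*Protocol article*

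**What the plan says.** The primary objective in the Objectives section is to find out whether the mailings "will decrease the proportion of patients who discontinue evidence-based secondary-prevention medications at twelve months post-STEMI". The Limitations section repeats that reading: "our primary outcome evaluates discontinuation", with persistence offered as another name for the same thing.

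The definition under Outcomes is different: "The primary outcome is the proportion of living patients who describe taking all cardiac medication classes of interest measured at twelve months". At twelve months the classes are statin, beta-blocker, ACE inhibitor or ARB, and aspirin. Nothing in the definition depends on what the patient took earlier. Eligibility adds no such condition either; beyond the stated criteria, "no other exclusion criteria will be applied".

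Participants and Setting gives the starting point from earlier data at the same unit: "While 78% of STEMI patients leave the HIU taking a statin, an ACE-inhibitor (or ARB), a beta-blocker, and aspirin". The same source puts four-class use at 63% at the 90-day point.

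On baseline data taken from the unit's registry, Data collection says: "This includes demographic information, comorbidities, and the findings at the time of angiography". Discharge medicines are not named.

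**The concern.** To discontinue a medicine, a patient must first have been taking it. Under the Outcomes definition, a patient who never received one of the four classes counts as a failure at twelve months, and a patient who starts the missing class later counts as a success. Neither is a discontinuation event. The objective and the definition therefore describe different quantities.

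What is at stake is the conclusion. If the trial is positive, the natural sentence, taken from the objective, is that letters reduced discontinuation. The measured outcome would support only that letters increased four-class use.

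The first planned medication measurement does not repair this. It is the three-month call, which comes after the one-month letter and the two-month postcard. On the protocol's own figures much of the loss has happened by then: 78% to 63% is 15 points, of the 28 net points between 78% at discharge and the 50% assumed for controls at twelve months.

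**Working it through.** **Inputs.** From Sample size: control proportion 50%, intervention 61%, two-sided 5% level, 80% power, variance inflation 1.02, 652 evaluable, 815 randomised. From Participants and Setting: 78% on all four at discharge, so 22% not. Assumed, because the protocol does not give it: x, the share of that 22% who are on all four at twelve months, taken from 0% to 50%. Also assumed: the 78% applies to the patients analysed in this trial.

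**Step 1, the plan's own figure.** With average proportion 0.555, n per arm = [1.960 × √(2 × 0.555 × 0.445) + 0.842 × √(0.50 × 0.50 + 0.61 × 0.39)]² / 0.11² = 319.2, so 320 per arm and 640 in all. Then 640 × 1.02 = 652.8 (stated 652), and 652 / 0.80 = 815. Power at 652 is 80.0%. The sample size is right for the outcome as defined, since 50% and 61% are proportions taking all four classes.

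**Step 2, how many control failures were not on all four at discharge.** Share = 0.22 × (1 − x) / 0.50.

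**Step 3, control persistence among the 78%.** (0.50 − 0.22x) / 0.78.

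**Step 4, adjusting the all-patient analysis for discharge status.** Let m = (0.555 − 0.22x) / 0.78, the average proportion on all four at twelve months among patients discharged on all four. Then R² = 0.78 × 0.22 × (m − x)² / (0.555 × 0.445). Effective n per arm = (326 / 1.02) / (1 − R²), and power is for 50% against 61%. This treats adjustment as a reduction in variance and is an approximation.

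**Step 5, analysing only patients discharged on all four.** 652 × 0.78 = about 509 patients. Case A: the whole overall effect falls in this group, so the difference there is 0.11 / 0.78 = 14.1 points. Case B: the difference within this group is 11 points.

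| x | Step 2: share of control failures | Step 3: control persistence | R² | Step 4: adjusted power, all patients | Step 5, case A | Step 5, case B |
|---|---|---|---|---|---|---|
| 0% | 44% | 64.1% | 0.35 | 94% | 94% | 76% |
| 10% | 40% | 61.3% | 0.24 | 89% | 93% | 74% |
| 25% | 33% | 57.1% | 0.11 | 84% | 91% | 72% |
| 30% | 31% | 55.6% | 0.07 | 83% | 90% | 71% |
| 50% | 22% | 50.0% | 0.00 | 80% | 89% | 70% |

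The mislabelling affects between about a fifth and just under half of control failures. Adjustment never takes power below plan over this range, but its gain fades as x rises. The restricted analysis has more or less power than the plan depending on where the effect falls, which the protocol does not say.

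**The case against.** The strongest defence is that outcome, hypothesis and sample size all concern patients taking the medicines, and agree with one another. Only the wording in two sections departs from them. Randomisation should balance discharge use, which is settled before the first letter, and the Outcomes section relies on this: "we anticipate that randomization will balance those patients for whom evidence is less clear or who might have contraindications to any of these medications". The all-comers design is a deliberate pragmatic choice, and the overarching goal is itself worded as long-term use. Patients discharged on two or three classes can still stop those, and the letters may prompt them to start others. All of this stands, and it means that the comparison of four-class use is valid. It does not turn use into discontinuation or separate fewer stops from more starts.

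The defence can also point to related analyses: class-by-class use at three and twelve months, stopping due to side effects, late-onset discontinuation among patients on all five classes with perfect adherence scores at three months, and possession ratios. These help only in part. The late-onset analysis is exploratory and conditions on a status measured after the letters began. The possession ratios cover only a sample aged 65 and older.

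Three stronger readings are tempting and are not supported:

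- **All 22% are failures.** Any of them on all four at twelve months is a success, and the figure comes from earlier registry data, not from this trial's patients.
- **Discharge medicines are unavailable.** The baseline list is introduced as what the registry information includes, in a condensed article, and earlier work at the unit did measure discharge prescribing.
- **Restricting to the 78% would gain power.** Case B shows that it can lose power.

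**Conclusion.** The point holds as a mismatch between the stated objective and the defined outcome. Followed as written, the trial can estimate an effect on use of all four classes at twelve months. It cannot attribute that effect to less discontinuation as opposed to more initiation.

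A reader might go further and infer that the trial cannot inform its objective at all. The documents do not support that: the contrast is randomised, correctly powered for what it measures, and relevant to the wider goal of long-term use.

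The size is 44% down to 22% of control-arm failures that need not reflect stopping a four-class discharge regimen. This rests on the 78% carrying over to this trial, the assumed 50% in controls, and an assumed 0% to 50% of the remaining patients being on all four at twelve months.

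**What to change.** 1. In Objectives and Limitations, describe the primary outcome as use of all four classes at twelve months, and keep the words discontinuation and persistence for analyses that condition on earlier use.
2. Record from the hospital record, for every randomised patient, whether each class was in use at discharge, if the registry does not already hold this.
3. Pre-specify being on all four at discharge as a covariate in the primary analysis, or at least in a supporting adjusted analysis.
4. Add twelve-month persistence among patients discharged on all four as a secondary outcome. Discharge status precedes the letters, so the comparison keeps the protection of randomisation. Make no claim that it has more power than the primary analysis.

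The cost is the wording changes and chart-extraction time for one set of baseline items per patient. The sample size need not change.
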